**Discussion:**

The main endpoint of the study will be the comparison of the diagnostic accuracy between ^18^F-SynVesT-1 and ^18^F-FDG PET in cognitive disorders with uncertain etiology and in exclusion of a neurodegenerative cause in patients with cognitive impairment in late-life psychiatric disorders. The strength of the relationship between cognition and imaging data will be assessed, as well as the potential incremental diagnostic value of including MR volumetry, ASL perfusion and rs-fMRI.

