The primary objective of this clinical trial is to determine the added value for clinical use of synaptic density imaging using a multimodal simultaneous PET/MR approach in patients with dementia and other patients developing cognitive dysfunction, by assessing the functional burden of the disease on the level of the synapse instead of synaptic activity/glucose metabolism, and by identifying an optimal combination of synaptic density and other PET/MR imaging metrics (perfusion, structural atrophy) that may allow early assessment and risk stratification for cognitive and behavioral dysfunction in de novo patients with uncertain origin of dementia. This will enable us to better understand the underlying pathophysiology of dementia, assess the direct consequences of underlying proteinopathy, relate this to subsequent structural measures and identify those parameters that can contribute to the accuracy of an early differential diagnosis. It will thereby aid the societal/economic challenge of earlier diagnosis, prognosis and biomarker development for more objective and more efficient monitoring of novel therapeutic trials. Secondary objectives are to assess how synaptic density is altered in the different cognitive disorders and how it correlates to specific symptomatology. Moreover, a direct comparison between ^11^C-UCB-J and ^18^F-SynVesT-1 in terms of distribution volume and standardized uptake value ratios (SUVR), including variability and noise levels will be conducted in HV.

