### Study hypotheses

The following specific research questions will be addressed:

(i)Can SV2A PET, using the novel tracer ^18^F-SynVesT-1, be approximated quantitatively by means of a simplified reference tissue model in HV and is it quantitatively comparable to ^11^C-UCB-J?(ii)Are there regional differences between SV2A PET and ^18^F-FDG PET and do the patterns remain unchanged versus HV?(iii)Can ^18^F-SynVesT-1 PET detect various forms of dementia as accurately as ^18^F-FDG PET?(iv)Does a combination of ^18^F-SynVesT-1 PET with MR-based markers of structural abnormalities and arterial spin labeling allow a better discrimination of different forms of dementia?

Based on literature and current knowledge, the following hypotheses are formulated:

(i)Healthy aging does not result in reduced synaptic density in adults up to 85 years. ^18^F-SynVesT-1 may show a better signal-to-noise ratio and at least equivalent utility for clinical applicability compared to ^11^C-UCB-J.(ii)Simplified quantification of ^18^F-SynVesT-1 PET is possible with white matter (centrum semiovale) as reference region [30, 53] or cerebellum as pseudo-reference region [42].(iii)Synaptic density and arterial spin labeling, as indirect marker of neuronal activity, are related in absolute terms in healthy agers, while regional differences are present that may affect the sensitivity of detection of pathological consequences.(iv)^18^F-SynVesT-1 PET allows accurate detection of patients with an underlying pattern specific for Alzheimer’s disease, frontotemporal dementia and Lewy Body disease, and can discriminate these neurodegenerative diseases from healthy aging and patients with cognitive impairment due to late-life psychiatric disorder.(v)^18^F-SynVesT-1 PET has non-inferior sensitivity and specificity of diagnosis in comparison to ^18^F-FDG PET.(vi)Non-invasive determination of absolute ^18^F-FDG glucose metabolism, ASL and SV2A (SUVR) allows discrimination of patients with late-life psychiatric disorder and neurocognitive disorders with highest accuracy for synaptic density imaging.(vii)Synaptic density PET is better correlated to memory and executive neurocognitive tests compared to ^18^F-FDG PET or ASL, especially in the frontal and medial temporal cortex.

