The evaluation will be done in 3 steps: firstly, referring physicians will be asked to provide suspected diagnoses and confidence scores at predefined moments during clinical workup. Secondly, anonymized scans (orthogonal images, 3D surface rendering and z-score images by comparison to in-house database as clinical routine / comparison to healthy control normal data) with core clinical information will be presented at regular intervals to 3 nuclear medicine physicians with variable experience but after a short reader training in healthy ^18^F-FDG and ^18^F-SynVesT-1 scans. They will provide an image-based diagnosis and indicate the corresponding level of certainty. The different visual readers will then provide a consensus protocol for each scan. After visual reading, also semiquantitative volume of interest- and voxel-based classifications will be carried out (for ^18^F-FDG, ^18^F-SynVesT-1, ASL and rMAPS). Lastly, data will be compared in terms of accuracy based on the consensus clinical diagnosis (about 6 months after ^18^F-FDG scanning). Consensus clinical diagnosis is based on initial clinical findings and evolution, CSF biomarkers (/ amyloid PET), sMRI and ^18^F-FDG PET results. Note that patient data analysis can only be initiated after the finalization of the healthy subject ^18^F-SynVesT-1 database (so z-score images can be obtained).Voxel-based morphology (VBM) and voxel-based cortical thickness (VBCT) analysis, adjusted for total intracranial volume will be used to assess structural gray matter volume and thickness differences in all subjects in the CAT12 toolbox of Statistical Parametric Mapping (SPM12). We will analyze individual imaging modalities (^18^F-SynVesT-1 and ^18^F-FDG PET, ASL, structural MR, rs-fMRI) independently in a univariate analysis to address the different modality, as well as using a multivariate approach as part of the underlying research questions.

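### Structural MRI helps set the consensus diagnosis and is also a marker whose added value is tested, so a volumetry gain scored against that diagnosis carries partial incorporation bias, probably in its favour

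*Protocol article*

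**What the plan says.** Under Data analysis and statistics, the protocol article says that "data will be compared in terms of accuracy based on the consensus clinical diagnosis (about 6 months after ^18^F-FDG scanning"). It then lists what that diagnosis rests on: "Consensus clinical diagnosis is based on initial clinical findings and evolution, CSF biomarkers (/ amyloid PET), sMRI", with FDG PET as the last item. Study participants adds that sMRI already feeds the initial working diagnosis, before referral for FDG PET and so before inclusion.

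Structural MR is also under test:

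- Study hypotheses, research question (iv), asks whether combining SynVesT-1 PET "with MR-based markers of structural abnormalities and arterial spin labeling allow a better discrimination of different forms of dementia".
- The Discussion paragraph of the Abstract lists among the aims "the potential incremental diagnostic value of including MR volumetry, ASL perfusion and rs-fMRI".
- The primary objective, in Background, includes "identifying an optimal combination of synaptic density and other PET/MR imaging metrics (perfusion, structural atrophy").
- Data analysis and statistics puts structural MR among the modalities analysed both univariately and multivariately, and measures it by VBM and cortical thickness in CAT12.

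The article describes no other reference standard for question (iv). The limitations in the main Discussion accept that FDG PET will probably influence the final diagnosis and favour FDG. They offer anonymized reads by physicians outside the work-up as the response. They do not mention sMRI in this connection.

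**The concern.** A marker that helps to set the reference diagnosis will agree with that diagnosis more often than it agrees with the disease. If the panel sees atrophy and leans towards a diagnosis because of it, a volumetric measure of the same brain predicts the panel's label partly for that reason. The increment of volumetry over SynVesT-1 then mixes true discrimination with built-in agreement, and the plan as written cannot separate the two.

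At stake is the part of the primary objective that seeks a best combination of synaptic density with other PET/MR measures. Volumetry could be credited with more added value than it has. This is distinct from the FDG bias that the article acknowledges, because taking FDG out of the reference would leave sMRI in it. It does not bear directly on the SynVesT-1 versus FDG comparison.

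**Working it through.** The plan states no figure on this point, so there is none to reproduce. The check has two parts.

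**1. Markers against the reference list**

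| Marker | Listed in the consensus diagnosis? | Role in the added-value questions |
|---|---|---|
| SynVesT-1 | No | Base marker |
| Structural MR | Yes (sMRI) | Added marker |
| ASL | No | Added marker |
| rs-fMRI | No | Added marker (Abstract) |
| FDG PET | Yes | Comparator |

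Of the markers added to SynVesT-1, only structural MR appears directly in the reference.

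**2. Possible size.** Every input here is an assumption; none comes from the protocol. The model has 400,000 simulated subjects, independent standard normal errors e1 to e4, and:

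- true disease D, with 50% prevalence
- SV2A marker S = 1.2·D + e1
- quantitative volumetry M = d·D + e2
- clinical sMRI read R = d·D + r·e2 + √(1 − r²)·e3, with r = 0.5 or 0.8
- all other clinical evidence C = 2.0·D + e4
- consensus label positive if C + w·R > (2.0 + w·d)/2, where w is the weight of sMRI
- gain = AUC(linear combination of S and M) − AUC(S)

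Gain in AUC; ranges run from r = 0.5 to r = 0.8:

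| d | Against truth | Consensus, w = 0 | w = 0.25 | w = 0.5 | w = 1 |
|---|---|---|---|---|---|
| 0 | 0.000 | 0.000 | 0.003–0.007 | 0.011–0.028 | 0.043–0.099 |
| 0.5 | 0.019 | 0.013 | 0.026–0.034 | 0.040–0.060 | 0.068–0.118 |
| 1.0 | 0.063 | 0.043 | 0.061–0.072 | 0.076–0.098 | 0.099–0.141 |

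Excess = consensus gain − true gain:

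| d | w = 0.25 | w = 0.5 | w = 1 |
|---|---|---|---|
| 0 | 0.003 to 0.007 | 0.011 to 0.028 | 0.043 to 0.099 |
| 0.5 | 0.007 to 0.015 | 0.021 to 0.041 | 0.049 to 0.099 |
| 1.0 | −0.002 to 0.009 | 0.013 to 0.035 | 0.036 to 0.078 |

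Two forces are at work. Errors in the label dilute any true gain, as the w = 0 column shows (0.043 against 0.063 at d = 1.0). Incorporation pushes the gain up. At d = 1.0 and w = 0.25 the two nearly cancel.

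**Cross-check with an extreme case.** Suppose PET is 80% accurate, MRI carries no true information, and the label simply copies MRI in a share f of patients (assumed). PET alone then has AUC 0.8(1 − f) + 0.5f, which is 0.740 at f = 20%. Given a positive label, the (PET, MRI) results (1,1), (1,0), (0,1), (0,0) have probabilities 0.42, 0.32, 0.18, 0.08; given a negative label, 0.08, 0.18, 0.32, 0.42. The combined AUC is 0.42(0.92 + 0.04) + 0.32(0.74 + 0.09) + 0.18(0.42 + 0.16) + 0.08(0.21) = 0.790. The gain is 0.790 − 0.740 = 0.050, when the true gain is 0. This lies inside the range above.

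**The case against.** The strongest reply is that the incorporation is only partial, and that stands. The consensus also draws on initial clinical findings, their evolution, CSF or amyloid PET, and FDG PET. A reader might infer that the volumetry gain is circular or wholly an artefact. The document does not support that, and the extreme case above needs an uninformative marker identical to the one in the label.

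Other points on that side:

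- **Different measures.** The sMRI in the work-up is a clinical examination made before FDG referral. The tested marker is quantitative VBM and cortical thickness, with the T1 scan acquired alongside SynVesT-1. Background notes that hippocampal volume is not widely quantified in routine care. The two are correlated, not the same. This stands, and it is why r is below 1.
- **Selection.** Patients enter because they remained uncertain after a work-up that included sMRI, which may limit its weight in the label. This is plausible, but the article neither quantifies it nor offers it as an offset.
- **Comparison with ASL and rs-fMRI.** A reader might infer that volumetry will be ranked unfairly above these. No such ranking is a stated analysis. ASL may also gain indirectly, since FDG is in the reference and Background cites a suggestion that ASL could replace FDG.
- **Scoring not spelled out.** The semiquantitative classifications listed before the accuracy comparison cover FDG, SynVesT-1, ASL and rMAPS, not structural MR. How the multivariate increment is scored may be set out in a document not shown. The point is therefore conditional on scoring against the consensus, which is the only reference the article gives.

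The reply does not remove the problem. Anonymized reads protect the reading of the index scans and leave the composition of the reference as it is.

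**Conclusion.** The concern holds as partial incorporation bias, probably in favour of volumetry. It is unacknowledged for sMRI, although the same mechanism is acknowledged for FDG. Its size cannot be estimated from the document. Under the assumed inputs the excess runs from about 0 to about 0.1 AUC. It is largest when volumetry is weakly informative (d of 0 or 0.5) and sMRI weighs heavily (w = 1), and near zero when volumetry is truly informative (d = 1.0) and sMRI weighs little (w = 0.25). These figures show direction and a plausible span; they are not a forecast for this trial.

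A reader might also take the gain against the full consensus as an upper bound on the true gain. That is not guaranteed: one scenario gives 0.061 against a true 0.063.

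**What to change.** Keep the consensus diagnosis as the reference for question (iv), and make four changes:

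1. Add a sensitivity analysis of the structural-MR increment for AD versus non-AD, defined by CSF or amyloid status in the patients who have it. This label does not use sMRI.
2. Report the ASL and rs-fMRI increments separately from the volumetry increment.
3. Name sMRI beside FDG in the limitations.
4. Describe any volumetry gain against the full consensus as likely inflated unless the sensitivity analysis supports it.

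The cost is mainly analysis and reporting text, since the CSF and amyloid data already arise in the work-up. The main Discussion makes retrospective subanalyses of these data subject to ethics approval, so that step may be needed.

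The sensitivity analysis has real limits. It answers one contrast, not the discrimination of several forms of dementia. On the planned subgroup sizes it would compare at most about 50 aMCI-AD patients with 20 + 20 + 20 = 60 pooled FTD, DLB and psychiatric patients, if clinical group and biomarker status agreed and all were tested. Not all will be: Study participants ties these tests to suspicion of AD, and the main Discussion expects lumbar puncture in most patients. The subset is therefore selected by who was tested.

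A consensus reached without sight of the MRI would address the bias more directly. Because sMRI precedes inclusion, it would need a separate blinded panel, so it is not proposed as the minimum.

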#### Sample size

Taking into account the test-retest variability for ^18^F-SynVesT-1 (5–10%) [52]; and a non-inferiority margin of 10%, assuming an α-level of 0.025 and a statistical power of 80%, the required sample size is 8 patients, of no ‘true’ difference. As sensitivity analysis, in case this difference would be 1% or 2%, sample sizes would increase to 10 and 12 per group.

Moreover, the sample size for brain receptor single-center PET studies using absolute quantification as we do in healthy subjects is typically between 10 and 20 in most literature studies. We include 40 healthy controls and 110 patients with estimated subgroups sizes of 50 amnestic mild cognitive impairment (aMCI)-AD, 20 FTD, 20 DLB and 20 patients with late-life psychiatric disorder based on our referral data.

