#### Recruitment

A total of 110 patients (M/F) will be recruited with uncertain diagnosis of cognitive impairment, as consecutively sent for ^18^F-FDG PET-MR imaging in their workup (estimated subgroup size: 50 patients with aMCI-AD; 20 patients with DLB; 20 patients with FTD; 20 patients with late-life psychiatric disorder). A minimal age was set at 30 years old, but the expected age ranges from 50 until +/- 85y old. The neuropsychological testing is expected to already be obtained during the diagnostic assessment. Some additional tests on top of those from the memory/referral clinic may be foreseen if necessary to ensure coverage of all relevant domains. The main sources of referrals constitute the UZ Leuven memory clinic of neurology, psychiatry, a collaboration with geriatrics and external hospitals situated in proximity of Leuven.

For the recruitment of HV, we will make use of (I) advertisements in targeted local journals and on the bulletin boards in the buildings of KU Leuven and UZ Leuven, on the websites of UZ/KU Leuven and in social media, and (II) of the volunteer database of the Center for Clinical Pharmacology. Forty screened HV (M/F) aged 18–85, approximately evenly spread over decades, will be included. These volunteers are screened for general good health condition (based on medical history, physical examination including vital parameters and clinical laboratory test and urinalysis), for neurocognitive and executive functioning via neuropsychological assessment, for amyloid status with amyloid PET scan (^18^F-NAV4694) if > 50y (below amyloid negativity is presumed) and for existence of other possible exclusion criteria.

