Statistical analyses will be performed using GraphPad Prism version 9 (GraphPad Software, La Jolla, CA). Demographic characteristics will be compared between groups using an unpaired Student t-test, unpaired Mann-Whitney U test, Fischer’s exact test or Chi-square test for trend as appropriate. Data normality will be verified by a Shapiro-Wilk test (α = 0.05). Correlation analyses will be performed by a Pearson correlation if data are normally distributed or by a Spearman correlation if data do not follow a normal distribution. Paired student’s t-tests or a non-parametric substitute will be performed in both a voxel-based and a VOI-based analysis to investigate regional differences between ^18^F-SynVesT-1 PET and ASL. Signature patterns of reduced synaptic density for different cognitive disorders will be assessed by comparing ^18^F-SynVesT-1 in patient subgroups versus HV using Student’s t-tests or Mann Whitney U-tests. To explore the diagnostic performance of ^18^F-SynVesT-1 compared to ^18^F-FDG, scans will be visually assessed by different specialists in nuclear medicine/neurologists and diagnostic accuracy (sensitivity, specificity and accuracy) as well as the interobserver agreement will be calculated. All results will be adjusted for multiple comparisons (Bonferroni) and investigated two-sided at a significance level of 0.05.

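### Comparing subgroups of 20 (or 50) patients with 40 volunteers by Student's t-test ties the error rate to an unchecked equal-variance assumption; naming Welch's test removes this at little cost

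*Protocol article*

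**What the plan says.** Under Data analysis and statistics, the protocol article compares ^18^F-SynVesT-1 "in patient subgroups versus HV using Student’s t-tests or Mann Whitney U-tests". The check that precedes the choice of test concerns distributional shape only: "Data normality will be verified by a Shapiro-Wilk test (α = 0.05"). Equality of spread is not mentioned. On error control the section states: "All results will be adjusted for multiple comparisons (Bonferroni) and investigated two-sided at a significance level of 0.05".

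The group sizes come from Sample size ("We include 40 healthy controls and 110 patients with estimated subgroups sizes") and Recruitment ("50 patients with aMCI-AD; 20 patients with DLB; 20 patients with FTD; 20 patients with late-life psychiatric disorder"). They are estimates from referral data.

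The article gives no between-subject SD for any group. The only variability figure under Sample size is for test-retest (5 to 10%), which is a within-subject quantity.

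**The concern.** Student's test estimates one common variance. When group sizes differ and variances differ too, the standard error is wrong. It is too small if the smaller group is the more variable, and too large if the larger group is.

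There is some reason to expect unequal spread. Volunteers are screened to be free of medical, psychiatric and neurological illness. Patients range from MCI to dementia, with several disease variants. If patients vary more, the three subgroups of 20 are tested too liberally and the 50 aMCI-AD patients slightly too strictly, all against the same nominal threshold. A Shapiro-Wilk test would not reveal this.

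At stake is the secondary objective in Background of describing how synaptic density is altered in the different disorders. Under unequal spread, the regions declared abnormal would partly reflect how group size and variance combine.

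**Working it through.** **Inputs.** From the article: 20 or 50 patients, 40 volunteers, two-sided 5%, Bonferroni. Assumed: normal data, equal means, a patient-to-volunteer SD ratio r from 0.67 to 2, and 40 regions for the Bonferroni illustration (level 0.05/40 = 0.00125).

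**Hand check at r = 1.5, volunteer SD = 1.** The test uses the expected squared standard error [((n − 1)r² + 39)/(n + 38)] × (1/n + 1/40). The true value is r²/n + 1/40.

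- 20 v 40: used (19 × 2.25 + 39)/58 × 0.075 = 0.1057; true 0.1125 + 0.025 = 0.1375. The standard error is too small by a factor √(0.1057/0.1375) = 0.877. The critical value 2.00 acts like 1.755, so the error is about 7.9%.
- 50 v 40: used (49 × 2.25 + 39)/88 × 0.045 = 0.0763; true 0.045 + 0.025 = 0.070. The factor is 1.044, the critical value 1.99 acts like 2.075, and the error is about 3.8%.

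**Full calculation.** Numerical integration over both sample variances gives the Student columns. At r = 1 it returns 5.0%, the article's stated level. Simulation agrees to within about 0.2 of a point. The Welch and Mann-Whitney columns are simulated.

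| r | Student 20 v 40 | Student 50 v 40 | Welch 20 v 40 | Welch 50 v 40 | Mann-Whitney 20 v 40 |
|---|---|---|---|---|---|
| 0.67 | 2.7% | 6.1% | 5.1% | 4.9% | 3.5% |
| 1 | 5.0% | 5.0% | 5.1% | 5.1% | 5.0% |
| 1.1 | 5.8% | 4.8% | – | – | – |
| 1.25 | 6.9% | 4.5% | 5.0% | 4.9% | 5.9% |
| 1.5 | 8.5% | 4.1% | 5.0% | 5.0% | 6.8% |
| 2 | 11.2% | 3.7% | 5.0% | 5.0% | 7.9% |

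**After Bonferroni, 20 v 40.** At nominal 0.00125 the per-test error at r = 1.25, 1.5 and 2 is 0.0026, 0.0045 and 0.0087. The relative excess grows in the tail: at r = 1.5 it is 8.5/5 = 1.7-fold at 5%, but 0.0045/0.00125 = 3.6-fold here.

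- 40 independent regions: 1 − (1 − a)^40 gives about 10, 16 and 30%.
- Common correlation 0.7 (simulated): about 4, 6 to 7 and 10%. With equal variances the same setting gives about 2.2%, because Bonferroni is conservative under correlation.

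**Power cost of Welch with equal variances.** For 20 v 40 and an assumed difference of 0.8 SD, power is about 81% against 82% for Student at 5%, and about 31% against 33% at 0.00125.

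**The case against.** The strongest reply is that the decisive input is missing from the article. No SD ratio is given, and the direction is open. Volunteers run from 18 to 85 ("Forty screened HV (M/F) aged 18–85, approximately evenly spread over decades, will be included"), while patients are expected from about 50 to 85, so volunteers could be the more variable group. The article's own hypothesis that healthy ageing does not reduce synaptic density weakens this reply but does not settle it. It stands as a limit on size and direction. It does not defend Student's test, which misses 5% either way.

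Four stronger readings are tempting, and the documents do not support them.

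- A reader might infer that the family-wise error is 30%. That needs r = 2 and 40 independent regions, all unaffected in mean yet more variable. Regional ratios within one brain share a reference region and should be correlated. Where disease widens the spread it probably lowers the mean too, and rejection there is not a false positive.
- A reader might infer false synaptic loss at these rates. The tests are two-sided, so about half of the false rejections would be apparent increases.
- A reader might infer that loss in AD is materially under-called. For 50 v 40 and a difference of 0.8 volunteer SD, at the 5% level, Student has 90.9% power against 91.7% for Welch at r = 1.25, and 82.6% against 84.7% at r = 1.5. The gap reaches about 5 points only at r = 2 or at strict Bonferroni levels. Unequal subgroup sizes make the extent of significant regions differ under any test.
- A reader might infer that voxel models or covariate regressions need repair too. The article describes neither for the signature-pattern comparison.

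It can also be said that Student's t-test may be a family name and that the variance form belongs in an analysis plan not shown here. That is possible. But the article names a test, and its standard meaning is the pooled one.

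**Conclusion.** The point holds as a minor one. With the planned sizes, the nominal 5% level is reached only if patients and volunteers are equally variable, which the article neither states nor checks. Departures are small at r = 1.1 and clear from about 1.3 upward. They reverse if volunteers vary more. The Mann-Whitney alternative is no cure at 20 v 40, and Bonferroni does not remove the excess.

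The conclusion rests on the pooled reading of the test name, on the estimated subgroup sizes being met, and on assumed SD ratios. The family-wise figures further depend on an assumed 40 regions and their correlation. The diagnostic-accuracy comparison, which the Abstract calls the main endpoint, is not touched.

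**What to change.** In Data analysis and statistics, replace Student's t-test by Welch's unequal-variance t-test for the patient-subgroup-versus-volunteer comparisons, and apply it without a preliminary test of variances. Because Welch holds about 5% in both directions, the change does not depend on knowing which group is more variable.

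The cost is one line of wording. If variances are equal, it also costs about 1 point of power at the 5% level and about 2 points at 0.00125. The article says that patient analysis cannot start until the volunteer database is complete, so the change fits naturally before that step.

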
Until recently, measuring synaptic density in humans required brain tissue from autopsy or surgical resection specimens. In vivo PET imaging of synaptic density has now become possible through development of radioligands with high affinity and selectivity for synaptic vesicle protein 2 A (SV2A) [25], which is the only of three isoforms that is ubiquitously and homogeneously located/expressed in synapses across the brain. ^11^C-UCB-J has been thoroughly validated and is regarded as best-in-class ligand for SV2A/synaptic density PET imaging. ^11^C-UCB-J shows good pharmacokinetics, quantification of ^11^C-UCB-J distribution volume is possible and is an vivo proxy of synaptic density [26, 27]. ^11^C-UCB-J has been used in clinical epilepsy drug trials [28]. Simplified quantification with a white matter reference is possible for easier use in patient populations [29, 30]. Furthermore, stability of synaptic density in healthy aging has been shown [31, 32]. A direct comparison in young HV, has shown differences between resting ^18^F-FDG uptake patterns and the regional distribution of synaptic density, with relative differences up to 30% with higher ^11^C-UCB-J signal especially in the hippocampus, lateral temporal cortex and cingulate, areas of particular importance in cognitive impairment [33].

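### The SynVesT-1 signature-pattern tests compare older patients with volunteers of all adult ages and cannot adjust for age; if SUVR changes with age, part of that change would be read as disease-related loss

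*Protocol article*

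**What the plan says.** The Recruitment section says of patients that "the expected age ranges from 50 until +/- 85y old", with a formal minimum of 30 years. It describes the 40 HV as "aged 18–85, approximately evenly spread over decades, will be included".

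Data analysis and statistics names the test for the SynVesT-1 signature patterns: "patient subgroups versus HV using Student’s t-tests or Mann Whitney U-tests". It gives no age covariate, no age matching and no age-restricted HV subset. The only covariate named in the article belongs to the structural MR analysis, which is "adjusted for total intracranial volume".

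The article does take a position on age. The Background says that "stability of synaptic density in healthy aging has been shown", in a paragraph on 11C-UCB-J. Study hypotheses then lists as hypothesis (i): "Healthy aging does not result in reduced synaptic density in adults up to 85 years".

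Readers are shown "z-score images by comparison to in-house database as clinical routine / comparison to healthy control normal data". The same section says that patient analysis must wait until the healthy-subject SynVesT-1 database is complete, so that z-scores can be made.

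**The concern.** A two-sample test of patients against HV estimates the disease effect plus whatever the age difference contributes. By design the two groups have different age distributions, and the named tests have no means of separating the two contributions. If regional SynVesT-1 SUVR declines with age, a region may enter a disease signature because the patients are older. If it rises with age, real loss may be hidden.

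The analysis at stake serves a secondary objective: how synaptic density is altered in each disorder. The effects sought are not all large. The Background puts neocortical SV2A change in Alzheimer's disease at about 10%, so a spurious few per cent matters there more than in the medial temporal lobe, where it cites up to 40%.

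**Working it through.** **The plan's own figure.** The article gives no figure for this comparison. Its sample sizes of 8, 10 and 12 come from a non-inferiority calculation with no age term. They reproduce as n = 2 × [SD × (1.960 + 0.842) / (10 − d)]² with SD 6.9%, which lies inside the stated 5-10%. For d = 0, 1, 2 this gives 7.47, 9.23 and 11.68, rounded up to 8, 10 and 12. They do not bear on the age question.

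**Inputs from the article.** HV: n = 40, ages 18-85, roughly even. Patients: expected 50-85, subgroups of 50, 20, 20 and 20. Tests are two-sided at 0.05.

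**Assumptions.** Ages are uniform within each range. The age trend is linear and the same in both groups. The between-subject SD is 10% or 15%. The slope is 0 to 3% decline per decade. The article gives neither slope nor SD, hence the range.

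**Age gap.**
- HV mean: (18 + 85)/2 = 51.5 years
- Patient mean: (50 + 85)/2 = 67.5 years
- Gap: 67.5 − 51.5 = 16 years, or 1.6 decades
- HV aged 50 or over: 40 × (85 − 50)/(85 − 18) = 20.9, about 21
- HV younger than 50: 40 × (50 − 18)/(85 − 18) = 19.1, about 19

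**Bias.** Spurious reduction = 1.6 × slope per decade.

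**False-positive rate.** 20,000 simulated trials per setting with no disease effect, one region, t-test at two-sided 0.05. Each cell shows SD 15% to SD 10%.

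| Slope per decade | Spurious reduction | 50 vs 40 | 20 vs 40 |
|---|---|---|---|
| 0 | 0 | 5% | 5% |
| 1% | 1.6% | 8-12% | 7-9% |
| 2% | 3.2% | 16-30% | 12-19% |
| 3% | 4.8% | 31-53% | 19-33% |

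**Hand check of one cell** (slope 2% per decade, SD 10%, 50 vs 40).
- HV variance: 10² + (0.2 × 67)²/12 = 100 + 15.0 = 115.0
- Patient variance: 10² + (0.2 × 35)²/12 = 100 + 4.1 = 104.1
- Standard error: √(115.0/40 + 104.1/50) = 2.23
- Standardised bias: 3.2/2.23 = 1.44
- Chance of exceeding 1.96: P(Z > 0.52) = 0.30, in line with the simulation

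**With age in the model.** The same data analysed by a linear model on group and age reject in 4-6% of runs (3,000 per setting) in every scenario.

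**z-scores, conditionally.** If SynVesT-1 z-scores used the whole HV set with no age adjustment, unaffected patients would have a mean z of 0 at slope 0. The mean would be about −0.1 to −0.2 at 1%, −0.2 to −0.3 at 2% and −0.3 to −0.4 at 3% per decade.

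**The case against.** The strongest reply is that the authors considered age: the Background cites work showing stable synaptic density in healthy ageing. If that carries over, the slope is zero, the bias is zero and the test keeps its 5% level. This stands as a condition on the finding. It does not remove the finding, for three reasons. The statement concerns 11C-UCB-J. The same proposition is a hypothesis of this trial. And patients are measured by SynVesT-1 SUVR with a reference region still to be chosen from the HV data; a ratio takes on any age trend in its denominator, so stable density would not guarantee a stable SUVR.

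A second reply is that a condensed article need not list covariates, and that an age-appropriate HV subset is not ruled out. That is fair for what the article leaves open. Here, however, it names specific tests, and those tests cannot adjust for age. The planned demographic comparison would reveal an age gap but not correct it. Partial volume correction deals with atrophy, which is only one route to an apparent age decline.

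Third, all results are to be Bonferroni-adjusted. This lowers the rates in the table but leaves the bias unchanged.

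A reader might infer more than the documents support:
- That the z-score images are not age-adjusted. The article is silent on this, and such pipeline detail may sit in the full protocol.
- That the reader maps would be shifted for SynVesT-1 but not for FDG. The age handling of the FDG database is not stated either.
- That ASL and grey-matter measures are compared across groups without age. The quoted test covers SynVesT-1 only, the ASL test described is a paired comparison with SynVesT-1, and naming intracranial volume for the structural analysis does not show that age is left out.

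**Conclusion.** The point holds in conditional form. The SynVesT-1 signature-pattern analysis sets groups with an expected mean age gap of about 16 years against each other by tests that cannot account for age, and it is protected only if SUVR does not depend on age, which this trial has yet to show. The possible bias is 1.6 times the slope per decade: nil at slope 0, and up to 4.8% at 3% per decade, about half of the 10% neocortical change cited for Alzheimer's disease. These figures rest on uniform ages and assumed slopes and SDs; the false-positive rates are for a single region before Bonferroni.

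It would go too far to say that age differences are certain to be counted as disease, because that presumes a non-zero slope. It would also go too far to say that the main diagnostic-accuracy comparison is compromised. That comparison scores image reads against the consensus clinical diagnosis, not these tests. The HV data could reach it only through the SynVesT-1 z-score images, whose age handling is unstated. The change is worth making but concerns a secondary analysis.

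**What to change.** Replace the two-sample tests for the signature patterns by a linear model of each regional or voxel SynVesT-1 SUVR on group and age, with sex as an optional further term. Repeat the comparison with HV aged 50 or over (about 21) as a sensitivity analysis; this also checks that the result does not lean on a linear trend carried over from younger volunteers. Apply the same age adjustment to any patient-versus-HV comparison of ASL or grey-matter measures.

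State how the SynVesT-1 z-score images handle age and, if this is not already done, derive them from age-adjusted HV values before patient reads begin.

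Age is already collected, so no extra scans or participants are needed. The cost is one degree of freedom for age, two with sex, and a little analysis work. If age has no effect on SUVR, little is lost.
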